**Fig. 1 Fig1:**
[figure not shown]
Time schedule of the RCT

**Fig. 2 Fig2:**
[figure not shown]
SPIRIT diagram depicting participant timeline

### Sample size

The sample size was calculated based on number of cases needed to identify an effect on time to (lasting) RTW. Based on previous research of RTW interventions for employees with psychological distress a hazard ratio (HR) was chosen of 1.8 [11, 12, 21]. A sample size calculation was performed with an HR of 1.8, alpha of 0.5 and power of 80%, which generated a total sample size of 144 participants, 36 participants per group. Accounting for a loss-to-follow up of 15% after 12 months, we aim to include 166 participants.

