Some previously evaluated interventions that aimed to facilitate RTW for employees with common mental health problems showed mixed results. An e-Health program to facilitate RTW based on psychological principles, such as psycho-education, cognitive behavioral therapy (CBT) and problem-solving therapy (PST) was effective on duration to first RTW (50 days) compared to conventional sickness guidance (usual care; 77 days). The e-Health program was not effective on lasting RTW [11]. A process evaluation of the e-Health program revealed that adherence of employees to the program varied between 13 and 90% [15], which might have impacted the full realization of the programs potential.

Another study evaluated the effectiveness of a Participatory Approach (PA) for employees on sickness absence with common mental disorders [12]. The PA is a stepwise process between the employee and his or her supervisor with the aim to reach consensus about obstacles and solutions to enable RTW, under guidance of a RTW-coordinator. Overall, the PA had no effect on lasting RTW, except for the subgroup of employees who indicated at baseline that they were open to RTW despite symptoms. For these employees, with a positive cognition towards RTW despite symptoms, the PA significantly reduced the time to lasting RTW (55 days) compared to conventional sickness guidance (usual care; 120 days) [12].

As the e-Health program was effective on first RTW – but not lasting RTW, and the PA was effective only for the subgroup who had a positive cognition towards RTW despite symptoms, we propose a stepped-care approach to combine these effective elements. The stepped-care approach starts with a low-intensive e-Health early in the absenteeism process. The e-Health consists of a tailored program which focuses on developing and reinforcing a positive cognition towards RTW. If RTW is not reached, the e-Health program is followed by a more intensive PA that has greater involvement of the workplace environment. The combination of these elements in a stepped-care approach aiming to facilitate a timely and lasting RTW is considered potentially effective. The aim of this paper is to describe the design of the RESTART (*R*eturn to work for *E*mployees with distress: a *ST*epped c*AR*e *T*reatment) study, which includes an evaluation of the effectiveness of the stepped-care intervention on lasting RTW by a randomized controlled trial and a process evaluation.

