### Randomization and blinding

Randomization takes place on employee level. In addition to usual care, participants can receive e-Health and/or PA. This leads to a 2 × 2 factorial design, which allows to test the main effects of e-Health and PA separately, as well as the combined effect on lasting RTW. Therefore, participants are randomized twice, which results in two comparisons in the main outcome analysis: PA vs. not PA and e-Health vs. no e-Health. On top of usual care participants receive either: (1) e-Health and PA, (2) e-Health only, or (3) PA only (see Fig. 1). A time schedule of enrolment, interventions, and assessments are presented in Fig. 2. Both randomizations take place directly after baseline to ensure even-sized groups. If, however, participants who are assigned to receiving PA (partially) returned to work before PA starts, they will not receive PA.

A computer-based randomization list, generated by an independent researcher, will be used to allocate participants, based on their participant-ID, to one of the four groups. Before the statistical analyses are performed the condition-IDs are recoded by an independent researcher, which allows the primary researcher to be blinded for the allocation and the RCT to be single-blind.

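### The sample-size paragraph prints alpha 0.5, which does not fit 144 participants at HR 1.8 and 80% power and is most likely a misprint for 0.05

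*Protocol article*

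**What the plan says.** The Sample size section bases the calculation on time to lasting RTW. On the effect, it says that "a hazard ratio (HR) was chosen of 1.8", with earlier trials of RTW interventions as the source. On the inputs, it says: "A sample size calculation was performed with an HR of 1.8, alpha of 0.5 and power of 80" per cent. The result is "a total sample size of 144 participants, 36 participants per group". The section then adds: "Accounting for a loss-to-follow up of 15% after 12 months, we aim to include 166 participants".

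It does not say whether alpha is one- or two-sided, how many events are needed, or what proportion of participants is expected to reach lasting RTW within 12 months.

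The Randomization and blinding section sets out "two comparisons in the main outcome analysis: PA vs. not PA and e-Health vs. no e-Health", and states that "Both randomizations take place directly after baseline to ensure even-sized groups". Each main effect is therefore a comparison of two equal halves, 72 v 72 among 144. The Data analysis section specifies Cox regression and gives no significance level. No other section gives one either, so nothing in the article corrects the printed 0.5.

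**The concern.** An alpha of 0.5 is ten times the conventional 0.05 and would make the required number of events very small. A total of 144 is much larger than such an alpha would normally produce at a hazard ratio of 1.8. So one of the printed figures looks wrong, and alpha is the obvious candidate.

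What is at stake is whether the justification of the sample size can be checked. For a time-to-event outcome, power depends on events. The number of participants follows from the number of events only through an assumed event proportion. With alpha misprinted and that proportion not given, a reader cannot tell which calculation produced 144, or how many events the trial must observe to have its stated power.

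**Working it through.** **Inputs from the article.** HR 1.8; power 80% (z = 0.8416); alpha 0.5 as printed; N = 144 before loss to follow-up; equal allocation for each main effect; follow-up 12 months.

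**Assumptions.** Sidedness is not stated, so both are tried. The event proportion is not stated, so the proportion that would make 144 correct is solved for, and power is shown over a range.

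**Formulas.**
- Schoenfeld, 1:1: D = 4(z_alpha + 0.8416)² / (ln 1.8)², with (ln 1.8)² = 0.3455.
- Freedman, as a cross-check: D = (z_alpha + 0.8416)² × (2.8/0.8)².
- Power with D events: Φ(√D × ln 1.8 / 2 − z_alpha).

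**Step 1: the printed alpha.** Two-sided 0.5 has z = 0.6745, so D = 4 × 1.5161² / 0.3455 = 26.6, or 27 events. One-sided 0.5 has z = 0, so D = 4 × 0.8416² / 0.3455 = 8.2, or 9 events.

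**Step 2: the event proportion needed for 144.**

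| Alpha | Events, Schoenfeld (Freedman) | As a share of 144 |
|---|---|---|
| 0.5 two-sided | 27 (29) | 19% (20%) |
| 0.5 one-sided | 9 (9) | 6% (6%) |
| 0.05 two-sided | 91 (97) | 63% (67%) |
| 0.05 one-sided | 72 (76) | 50% (53%) |

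Before rounding up, the first Schoenfeld entry is 26.6/144 = 18.5%, hence about 18 to 20%.

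**Step 3: is about 20% credible?** The only guide in the article is in its Background, from a subgroup of an earlier trial: "the PA significantly reduced the time to lasting RTW (55 days) compared to conventional sickness guidance (usual care; 120 days". If 120 days is read as an exponential median, the proportion with lasting RTW by day 365 is 1 − 2^(−365/120) = 0.88. This is weak evidence: the subgroup was selected for a positive attitude to RTW, and the article does not say that the figure is a median. Still, it points far above 20%.

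**Step 4: power at the printed alpha.** If 50% of 144 have the event (72 events), √72 × 0.5878 / 2 = 2.494. Then Φ(2.494 − 0.6745) = 0.966, about 97%. At 100% events it is 99.8%. Neither is 80%.

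**Step 5: power of 144 at two-sided 0.05.** 50% events (72): Φ(2.494 − 1.960) = 70%. 63% (about 91): 80%. 80% (about 115): 88%. 100% (144): 94%.

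**Step 6: the later figures.** 4 × 36 = 144, and 144 × 1.15 = 165.6, which rounds up to 166. Neither step involves alpha, so they do not show which alpha was used.

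**The case against.** The strongest reply is that this is a dropped zero. At 0.05 the total of 144 corresponds to a sensible event proportion, and nothing shows that recruitment or analysis rests on 0.5. A condensed article may also leave the event proportion to the full protocol or SAP. Much of this stands. The misprint is the likely explanation, and the missing proportion would not be a finding by itself. It matters here because, with alpha wrong, nothing else in the paragraph lets the reader work back to the intended calculation.

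One could also ask whether 0.5 fits some other target. For a pairwise comparison of 36 v 36, 27 events would be 27/72 = 37.5%. For an interaction of the same size, four times the events (4 × 27 = 108) would be 108/144 = 75%. But the article names the two main effects as its main outcome comparisons, and the sample-size paragraph mentions neither alternative.

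Four stronger readings are tempting, and the article does not support them:

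- *That 0.5 is the trial's decision threshold.* It appears only as an input to the sample size. The Data analysis section sets no threshold, and the SAP may.
- *That an ineffective intervention would be called effective half the time.* Even if 0.5 were used for testing, that holds only one-sided. Two-sided, a null intervention would be declared beneficial 25% of the time and harmful 25%.
- *That the chance of a false positive across the two main effects is 75%.* 1 − 0.5² = 0.75 counts every rejection, including harm, and assumes independent tests. False claims of benefit would come to 1 − 0.75² = 44%. Both figures depend on testing at 0.5, which the article does not say.
- *That two-sided 0.05 is shown to be the value behind 144.* The 63% is solved from 144, so the match is circular. One-sided 0.05 with 50% events gives 72/0.50 = 144 equally well.

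**Conclusion.** The point holds as an error in a stated figure. For a main-effect comparison at HR 1.8 and 80% power, alpha 0.5 agrees with 144 only if about 18 to 20% of participants (6% one-sided) reach lasting RTW within 12 months. That is well below what the article's own background figures suggest. The conclusion rests on the standard event formulas, on the main effect being the target, and on an event proportion clearly above 20%.

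A misprint for 0.05 is the most likely cause, but the sidedness and event proportion that were used cannot be determined from the article. No shortfall in power is shown: at two-sided 0.05, power is below 80% if fewer than about 63% reach lasting RTW and above it if more do, and the article does not say which was expected. No inflated error rate in the analysis is shown either.

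**What to change.** In a published correction, or in the SAP with a reference to this paragraph:

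1. Replace 0.5 with the alpha actually used, presumably 0.05.
2. State whether it is one- or two-sided.
3. State the target number of lasting-RTW events per main-effect comparison, and the 12-month lasting-RTW proportion that turned it into 144.

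These figures should come from the sponsor's own calculation and not be solved back from 144. If two-sided 0.05 was used, the target is about 91 events per main-effect comparison. It would then help to report that 144 participants give about 70%, 80% and 88% power at 50%, 63% and 80% events.

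The cost is one or two sentences. Design, recruitment and data collection need not change, unless the recovered calculation turns out not to support 144.

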#### Data analysis

Descriptive statistics will be provided for all relevant variables at baseline. To investigate the effectiveness of the interventions of the stepped care approach on lasting RTW a cox-regression will be conducted. To determine the effect of e-Health separately, the group who received [e-Health and PA] will be combined with the [e-Health only] group, and compared to the control- and [PA only] group. The same logic applies to PA; the PA groups will be combined and compared to the control- and [e-Health only] group. To test whether the combination of e-Health and PA in a stepped-care approach is superior to the separate interventions alone, we will study the interaction between PA and e-Health. For the secondary outcomes, depending on the type of outcome measure (continuous/categorical) generalized linear models or mixed effects logistic regression will be used. Analyses are conducted both unadjusted and adjusted for potential confounders. Additionally, effect modification of several factors, such as the (severity of) stress-related symptoms and cognition towards RTW despite symptoms, will be investigated by using interaction terms.

All analyses will be performed according to the intention-to-treat principle (ITT), which implies that all employees are analyzed according to the group they were assigned to, regardless of whether they actually received the intervention.

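### The target of 166 does not keep 144 participants after a 15% loss: 166 leaves about 141, and keeping 144 needs 170 (a minor error in one sentence)

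*Protocol article*

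**What the plan says.** The Sample size section bases the calculation on time to lasting return to work. Of the effect it says that "a hazard ratio (HR) was chosen of 1.8", and the other inputs are printed as "alpha of 0.5 and power of 80"%, "which generated a total sample size of 144 participants, 36 participants per group". The next sentence turns that requirement into the enrolment figure: "Accounting for a loss-to-follow up of 15% after 12 months, we aim to include 166 participants". The inflation formula is not shown, and no other section gives a different loss rate, target or inflation rule.

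Two other sections bear on the point. Recruitment and procedures keeps enrolment open until the needed number has been reached, so this figure decides when recruitment ends. Data analysis gives the primary method: "To investigate the effectiveness of the interventions of the stepped care approach on lasting RTW a cox-regression will be conducted".

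**The concern.** An allowance for loss to follow-up is meant to leave the required number once the stated fraction has gone. The fraction applies to those recruited, so the requirement is divided by one minus the loss. Multiplying the requirement by one plus the loss is a common slip and always gives too small a number. Here the enrolment figure equals the result of that multiplication.

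What is at stake is whether the sentence is true. A reader is told that 166 allows for a 15% loss from 144, and it does not. Because recruitment runs up to this figure, enrolment would close slightly before the plan's own stated requirement is covered.

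**Working it through.** **Inputs**, all from the Sample size section: required number 144 (4 × 36); loss to follow-up 15%; target 166.

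**1. Reproduce the printed target.**
- Required number × (1 + loss) = 144 × 1.15 = 165.6, rounded up to 166. This matches exactly.
- That the authors worked this way is an inference from the match. Steps 2 to 4 do not depend on it.

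**2. What 166 leaves at the stated loss.**
- Recruited × (1 − loss) = 166 × 0.85 = 141.1, so about 141.
- Shortfall: 144 − 141 = 3 participants with complete follow-up.

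**3. What would keep 144.**
- Required number / (1 − loss) = 144/0.85 = 169.4, rounded up to 170.
- Check: 170 × 0.85 = 144.5, which is at least 144.
- The printed target is 170 − 166 = 4 too low (4/170 = 2.4%).

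**4. The loss that 166 does cover.**
- (166 − 144)/166 = 22/166 = 13.3%, against the stated 15%.

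**5. Does this translate into power?** Not from the document's own figures: it gives no event proportion and no sidedness, and alpha is printed as 0.5. The following is therefore an illustration under assumptions: two-sided alpha 0.05, hazard ratio 1.8, a 1:1 comparison and the Schoenfeld formula, power = Φ(√events × ln 1.8 / 2 − 1.96).
- These assumptions need 91 events for 80% power. If 144 fully followed participants supply them, the event proportion is 91/144 = 63.2%.
- (a) Lost participants contribute nothing: 141 × 91/144 = 89.1 events and 79.2% power, against 80.1% with 91 events.
- (b) Lost participants are censored when they leave. Take exponential event times with 63.2% events by 12 months (rate about 1.00 per year) and independent exponential dropout reaching 15% by 12 months (rate −ln 0.85 = 0.1625 per year). The proportion with an observed event is 1.00/1.1625 × (1 − e^(−1.1625)) ≈ 0.591. Then 166 × 0.591 ≈ 98 events, and power is about 83%.
- Under model (b), for event proportions from 50% to 85%, 166 recruits yield more events than 144 fully followed participants would, and the number needed to match 144 is about 152 to 155.

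The head-count error is therefore certain, while the sign of any effect on power depends on how lost participants are treated.

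**The case against.** The strongest defence is that a head count is the wrong currency for a time-to-event outcome. A participant lost before month 12 stays in the Cox regression until censoring, and counts as an event if lasting return to work came first. The Outcome measures section adds that permission was requested to obtain the absence data from the occupational health service, so someone who stops filling in diaries need not be lost for the primary outcome. Under ordinary censoring assumptions 166 is enough, as model (b) shows. This stands, and it rules out one inference that a reader might draw: that the trial falls below 80% power, to about 79%. That figure holds only if every lost participant contributes nothing, and it needs an alpha and an event proportion that the document does not supply.

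A reader might also infer that 166 is wrong because it does not divide by four, given 36 per group and the statement "Both randomizations take place directly after baseline to ensure even-sized groups". The document does not support that either. The main analysis consists of two pooled comparisons, and 166 can split 83 against 83 on both factors, for example as 42, 41, 41 and 42. The figure of 36 per group belongs to the 144, and even-sized groups need not be exactly equal. No target beyond 170 follows from this.

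The gap is also small, 3 participants on the retained number and 4 on the target. That limits its importance but does not make the sentence right: the authors chose 144 as the number to protect and 15% as the loss, and 166 does not protect it.

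**Conclusion.** The point holds as an arithmetic error of minor weight. On the section's own figures, "we aim to include 166 participants" does not account for a 15% loss from 144: it leaves about 141 with complete follow-up, and it keeps 144 only up to a 13.3% loss. The number that keeps 144 is 170. This rests on no assumption beyond reading the 15% as a share of those recruited, which is its ordinary meaning. The multiplication by 1.15 is the likely cause but is inferred.

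No fall in power is claimed, and no analysis or conclusion of the trial changes. The 144 itself is not confirmed here, because it cannot be reproduced without an event proportion and a usable alpha.

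**What to change.** Restate the sentence in one of two ways:

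- Keep 166 and say that it leaves 141 participants with complete follow-up at a 15% loss, or equivalently that it keeps 144 up to a loss of about 13%.
- Give 170 as the number that keeps 144 after a 15% loss (144/0.85).

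The first costs one reworded sentence and no extra recruitment. The second costs the same sentence and 4 more participants. Either is acceptable given the size of the gap. The wording should say complete follow-up rather than imply that participants who are lost drop out of the Cox analysis.

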### Interventions

All participants receive usual care which consists of conventional sickness guidance by the OP, following the guidelines of the Netherlands Society of Occupational Medicine (NVAB). All guidance within the interventions (e-Health and PA) are performed by trained RTW-coordinators. Three OH practitioners received a one day training by the researchers in this role.

#### e-Health intervention

The e-Health intervention is based on the original Return@Work intervention [11], and adjusted according to the guidelines for common mental disorders of the Netherlands Society of Occupational Medicine [22]. After completing the baseline assessment, employees allocated to the e-Health group will receive access to the e-Health app. The employee is provided with a personal log-in code for the app. The e-Health application starts with an introduction on how to use the app and asks for the necessary permissions of the employee. Following this, the employee answers two navigating questions. The first navigating question is whether or not the employee believes he/she can return to work despite symptoms (cognition of RTW). If this question is followed by a negative answer (i.e. maybe/probably not/no/don’t know), this will be taken as an indication of a negative cognition towards RTW – and the program will include extra exercises to create and reinforce a positive cognition towards RTW. The second navigating question is if the employee labels his/her complaints as more “psychological” or more “physical”. In certain cases, employees with psychological distress categorize their complaints as primarily physical rather than psychological. In such cases, using psychological terminology usually doesn’t resonate with that employee’s experience which can lead to a lower adherence to the program. Therefore, if the employee labels their complaints as more physical, the information that is provided in each module will also be in terms of physical complaints.

Based on the scores of the 4DSQ and the navigating questions, the employee receives specific modules tailored to their needs.

The e-Health app includes the following modules:

Psycho-education on the relationship between psychological distress and RTW.Exercises aimed at creating and/or reinforcing a positive cognition towards RTW despite symptoms, based on cognitive behavioral principles.Psycho-education on pain and fatigue and the relationship with psychological distress, work and RTW. Exercises are based on relaxation principles.A task-analysis of all activities the employee performs in his/her work, and in which of these activities they foresee/experience obstacles for RTW.Problem-solving exercises specifically for the process of RTW. The steps include defining problems and goals, learning and applying problem-solving skills and developing more control of a problem-situation.Preventing relapse, aiming to make the employee more aware of personal distress signals that could increase the likelihood of loss of control.

The total duration of the e-Health is 6 weeks. Based on the findings of the process evaluation of Return@Work [15] and previous research about engagement in e-Health [23], employees will be stimulated to engage with the e-Health application to increase the likelihood that the employee will complete the program within 6 weeks. These means include timely notifications and reminders, personal progression of the modules and “achievements” after finishing modules, and the possibility to have a 30 min consult with one of the OH practitioners during the e-Health program.

